#### Digital platform

A comprehensive digital platform is being developed through [name]’s Wellcome Trust Principal Research Fellowship-funded PRIDE project: https://www.phfi.org/news-and-events/key-projects/pride. The PASS + intervention is already utilising digital technology to deliver the intervention through video-feedback on tablet computers; the integration of other elements into the PRIDE digital platform will be a major output of the formative phase and a key innovation within this scale-up project. It will allow remote supervision, peer therapy support and targeted training over three separate 3-day periods, with subsequent practice learning and supervision. This platform will thus successfully transition PASS and PASS + into a scalable m-health platform for delivery within existing health systems of an individualised intervention (which is the only kind that has shown success in this complex disorder).

#### Dosage

Families will undertake up to 12 face-to-face communication sessions over 8 months with the COMPASS Counsellors, along with 30 min daily home practice between sessions. PASS and PASS + pilot RCT data have demonstrated the feasibility, acceptability and pilot effectiveness of a 12-session intervention in this environment [9, 10]. Parents will also be offered the Plus modules which address coexisting problems as per the PASS + intervention protocol.

#### Fidelity

All therapy sessions will be audiotaped for the purposes of monitoring fidelity. Variability due to therapist effects will be minimised by frequent clinical supervision. Five percent of randomly selected sessions for each COMPASS counsellor will be formally coded for fidelity against the treatment manual over the course of the study by the UK team using the model successfully used in PASS and PASS + . The unique practice platform we will develop for COMPASS will ensure the highest level of fidelity of the intervention delivery and promises to be the most feasible evidence-based approach for scale-up in LMIC settings.

### Criteria for discontinuing or modifying allocated interventions {11b}

Decision to discontinue trial intervention will be taken by the research team if a serious adverse event (SAE) and/or multiple adverse events (AE), possibly or definitely related to the intervention, were reported by participants, or otherwise for the welfare or safeguarding of participants, where participation is no longer in their best interests. An adverse event will be considered serious when there is participant’s or caregiver’s death, a life-threatening injury requiring hospitalisation, prolongation of hospitalisation, significant disability/incapacity, congenital anomaly or requirement of intervention to prevent permanent impairment or damage. We do not anticipate any SAEs to relate to the trial intervention. Participants can also withdraw from the intervention programme and/or the trial at any time without the need to give any reason. The research team will keep an updated log of all withdrawals with relevant dates and details of reason for withdrawal. Participants will not be replaced and all data collected up until the point of withdrawal will be used unless participants explicitly request removal of their data from the trial.

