### Service use

The Cost of Illness Inventory (COII) captures costs related to education, childcare, relocation, healthcare contacts (outpatient, inpatient, medical emergencies, investigations and medication), religious retreats and rituals, specialist equipment, workshops and training, special diet, support and care, certification, occupational adjustments and government rebates/schemes [23].

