#### Hybrid evaluation schedule

Majority assessments that were earlier administered in person were planned to be conducted via telephonic interviews. Audio records of informed consent were taken. Detailed procedures were developed for secure storage and sharing of consent information. There were no changes in outcome measures of the trial; however, for ascertaining eligibility in terms of age equivalence, the motor skill domain of Vineland 3 was used as a replacement for Mullen Scales of Early Learning. The RAFIN was dropped given its relative difficulty with administration over phone. A COVID-19 Impact Questionnaire was added to understand the impact of the pandemic and associated lockdowns on the trial families. All assessments were planned over five contacts—four telephonic and one in-person (preferably in the office, if not, then at participant’s home).

Adequate precautions including routine sanitisation of assessment rooms and kits before and after assessments, providing sanitised office transportation to participants, regular temperature checks of all team members and visiting families, supporting COVID-19 tests and vaccination of team members and use of transparent masks during in-person assessments were taken to minimise exposure to COVID-19 for both participants and assessors.

Adapting the evaluation plan allowed trial assessments to continue in a situation where home visits in the community were not possible. Telephonically contacting families reduced the chances of exposure to COVID-19. However, in situations where telephonic interviews were not possible and there was mutual agreement to undertake home visits, assessors visited participants in communities. This has particularly been possible in the second quarter of 2022 which has seen reduction in COVID cases in the NCT of Delhi. Furthermore, continuing evaluations also ensures maintenance of competency of the trained assessors.

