### Adverse event reporting and harms {22}

We will collect information about adverse events at each follow-up visit and record adverse events in a standard format. Adverse events will be monitored by the DMEC and TSC. Serious adverse events (SAEs) will be reported to the project management group and sponsor. If any of the SAEs are a suspected unexpected reaction to the therapy (it is acknowledged that this is highly unlikely in this trial), these will be reported immediately to the sponsor, ethics committee and DMEC.

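### The printed definition of a serious adverse event ties first hospital admission to life-threatening injury but lists prolonged admission on its own, so some illness admissions would go unreported as SAEs

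*Protocol article*

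**What the plan says.** The only definition of seriousness in the article is in Criteria for discontinuing or modifying allocated interventions {11b}. It opens with "An adverse event will be considered serious when there is participant’s or caregiver’s death", continues with "a life-threatening injury requiring hospitalisation, prolongation of hospitalisation, significant disability/incapacity", and closes with "congenital anomaly or requirement of intervention to prevent permanent impairment or damage".

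The same section gives two grounds on which the research team may stop the intervention. One is event-based: "if a serious adverse event (SAE) and/or multiple adverse events (AE), possibly or definitely related to the intervention, were reported by participants". The other needs no event classification: "or otherwise for the welfare or safeguarding of participants, where participation is no longer in their best interests".

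Adverse event reporting and harms {22} sets the routes. "Serious adverse events (SAEs) will be reported to the project management group and sponsor". SAEs suspected to be unexpected reactions to treatment go at once to the sponsor, ethics committee and DMEC. Adverse events in general, with no seriousness threshold, are monitored by the DMEC and TSC. The adverse event form, described under COVID-19 Impact Questionnaire, covers any safety concern.

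Separately, Service use says the Cost of Illness Inventory (COII) records "healthcare contacts (outpatient, inpatient, medical emergencies, investigations and medication". Cost-effectiveness analysis places it at baseline, 9 and 15 months.

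**The concern.** Life-threatening event and hospitalisation usually stand as separate criteria for seriousness. Here they are merged into one item that is also limited to injury. The list then treats prolonging a hospital stay as serious in its own right, although the stay being prolonged need not have been serious. The two items do not fit together.

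The wording matters because seriousness is the first gate in {22}. An event classed as non-serious is not sent to the project management group and sponsor as an SAE. It also cannot enter the immediate route, which opens only for events already classed as SAEs. An illness admission suspected of being related to treatment could therefore miss the immediate route on wording alone.

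Admissions for illness are foreseeable in this population. Eligibility criteria {10} exclude a child with epilepsy only after a recent seizure, within 6 months. Hybrid evaluation schedule describes precautions to "minimise exposure to COVID-19 for both participants and assessors". At stake is an SAE count that is too low because of a phrase, in a trial that describes itself as low-risk under Provisions for post-trial care {30}.

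**Working it through.** The article gives no figure for this point, so there is none to reproduce. The check applies the printed list to types of event under three readings:

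- **Literal:** the words as printed.
- **Comma restored:** a separator is assumed to be missing after the word for injury, so that hospitalisation stands alone.
- **Separated:** life-threatening event, and hospitalisation or its prolongation, each stand alone.

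Unless stated, the event meets no other criterion in the list.

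| Event | Literal | Comma restored | Separated |
|---|---|---|---|
| Life-threatening injury, admitted | serious | serious | serious |
| Any admission that is then prolonged | serious | serious | serious |
| Illness admission, not life-threatening | not serious | serious | serious |
| Life-threatening illness, admitted | not serious | serious | serious |
| Injury admission, not life-threatening | not serious | serious | serious |
| Life-threatening illness, not admitted | not serious | not serious | serious |

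Three things follow.

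1. The literal and comma-restored readings classify the same admission in opposite ways (rows 3 to 5). Staff working from this sentence could apply either.
2. A missing comma does not repair the sentence fully. The life-threatening criterion would still cover injury only (row 6).
3. The caregiver is named only for death. Whether a caregiver's admission or disability can be an SAE is not stated.

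The reporting consequences of a non-serious classification, taken from {11b} and {22}:

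| Route | Depends on SAE status? | Effect |
|---|---|---|
| Report to project management group and sponsor | yes | lost as an SAE report |
| Immediate report to sponsor, ethics committee and DMEC | yes, and on a suspected unexpected reaction | lost only for events suspected to be such reactions |
| DMEC and TSC monitoring of adverse events | no | kept |
| Discontinuation on welfare or safeguarding grounds | no | kept |
| Event-based discontinuation | partly, and requires possible or definite relatedness | no change for unrelated events |

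On size, the document gives no admission rate. Purely as an illustration, assume that 2% to 10% of children are admitted per year. With 261 randomised and 15 months each, exposure is 261 × 1.25 = 326 child-years. Then 326 × 0.02 = 6.5 and 326 × 0.10 = 32.6, or about 7 to 33 child admissions. This is the number whose classification might have to be looked at, not the number missed. It overstates exposure, because 30 participants were already lost to follow-up by 31 March 2023 (Trial update as on March 2023). Some of these admissions would also be serious under another criterion. The finding does not depend on it.

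**The case against.** The strongest reply is that this is compressed wording. A free-standing item for prolongation makes most sense if hospitalisation was also meant to stand alone. The text is a journal article on protocol version 4, and neither that protocol nor the operating procedures are shown. This is a fair account of how the sentence may have arisen, and it limits the finding to the article's text. It does not remove the finding. The article prints what appears to be a full list, down to congenital anomaly, so this is a rule stated wrongly and not a detail left out.

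A reader might infer more than the text supports:

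- **That admissions for seizures, COVID-19 or caregiver mental illness can never be serious.** They can. Death, prolongation, disability and intervention to prevent lasting impairment need no injury, although for caregivers only death is clearly covered.
- **That such admissions escape oversight.** They do not. The DMEC and TSC monitor adverse events of any seriousness, the form covers any safety concern, and the sponsor audits annually under {23}.
- **That one such event cannot open a discontinuation decision.** The welfare and safeguarding ground needs neither seriousness nor several events. The event-based ground requires relatedness, so many of these admissions would not meet it even if classed as serious.
- **That all of them are kept from the ethics committee by the wording.** Immediate reporting applies only to suspected unexpected reactions. An unrelated admission would not take that route under any definition.
- **That a stated share of admissions is missed.** Any such share would only restate an assumed rate.

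The article also describes no link between the COII and SAE reporting. In a condensed article that silence is not an error. The COII matters here only as an existing source for a check.

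**Conclusion.** The point holds in a limited form. As printed, {11b} ties both first hospitalisation and the life-threatening criterion to injury, and this does not fit its own separate item for prolongation. Followed literally, an illness admission that meets no other criterion is a non-serious event. It is not reported as an SAE to the project management group and sponsor, and it misses the immediate route if suspected to be a related and unexpected reaction. The reported SAE count would then be too low.

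The amount cannot be estimated from the document. The conclusion rests on two assumptions: that staff apply the printed words, and that the full protocol does not define seriousness differently. The primary efficacy analysis is not affected. The point is worth settling before database lock because correction is cheap. At 31 March 2023 only 86 of 261 follow-up assessments (33%) were complete, and {20a} places all analysis after the 15-month data.

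**What to change.** First, check version 4 of the full protocol. If it already lists the criteria separately, confirm that and correct the article. Otherwise:

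- Reword the definition of seriousness used for reporting so that life-threatening event, and hospitalisation or its prolongation, stand as separate criteria. Keep every remaining item, including congenital anomaly.
- State which criteria apply to caregivers as well as children.
- Reconcile the wording with {22} and with the discontinuation text in {11b}. How the clarified definition bears on stopping the intervention is for the investigators to settle, and no stopping rule is proposed here.
- Before database lock, re-classify the adverse event forms already collected under the clarified definition.
- List the children's inpatient and emergency entries in the COII, in both arms, against the SAE log. Assess each unmatched entry individually. Entries should not be converted to SAEs automatically, because planned admissions, for example, are not adverse events.

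The cost is one reworded sentence, one pass over existing forms, and one data listing with individual review. No new visits or participants are needed. The drawback is some extra review work and a higher reported SAE count, probably made up mostly of events unrelated to the intervention.

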#### Pandemic-related modifications

Changes have become necessary due to the unprecedented COVID-19 restrictions in India in general and Delhi in particular, during the course of the trial—which made it impossible to deliver the planned face to face sessions, either in the participant’s homes or in any other setting. Moreover, the future pattern of social life in the medium term is unclear in India as it is internationally. From June 2020, an online/remote option for delivery of the PASS Plus intervention has been initiated with practice cases. This is through videoconferencing technology or where this is not possible due to lack of internet availability or access to a smartphone, by telephone. The default mode of intervention delivery will still be face-to-face when possible, but (as with now many health interventions internationally) we need to develop the capacity for a blended model including online remote delivery when needed.

Parents will be taught how to record and upload/send parent–child interaction play videos in advance of the first remote session. Where necessary, an additional introductory session will be included to ensure parents are familiar with and comfortable using the required technology. These procedures have been developed during the recent virtual delivery of this intervention to nine practice families outside the trial. We have found that the process has been acceptable and feasible for parents and therapists for most sessions delivered. They have also given positive feedback on becoming more proficient with using the various digital applications because of the intervention. Regarding supervision, we have found that the transfer of knowledge of strategies appears to be taking place as well as it would have in a face-to-face session.

Making these immediate changes will allow families to continue/commence the intervention, despite the restrictions imposed by COVID-19 lockdowns. Should this online delivery prove successful and acceptable and should the unfolding situation require it, we will then be able to consider future-proofing the trial over the medium and longer term to allow the trial to complete in the face of an uncertain situation. This would then have the further added value of future-proofing the intervention itself for work at scale in India, when it may well be (as internationally) that remote working becomes a standard option for healthcare delivery in the future.

### Strategies to improve adherence to interventions {11c}

See below under ‘Response to COVID-19 pandemic’.

### Relevant concomitant care permitted or prohibited during the trial {11d}

Participants within the intervention and TAU will be permitted to access any concomitant care or intervention.

### Provisions for post-trial care {30}

There are no provisions for post-trial care. COMPASS is a low-risk trial, and no significant harm is anticipated for participants during the course of this trial. There is no provision of compensation to those who suffer any harm from trial participation.

## Outcomes {12}

### Primary outcome

The primary outcome is as follows: autism symptom severity assessed at 9 months post randomisation using the Brief Observation of Social Communication Change (BOSCC) [16], a blinded researcher symptom-coding from video-taped child-researcher interaction. BOSCC is an adaptation of the standard diagnostic symptom algorithm to (i) maximise sensitivity to symptom change in treatment studies, with codes combining symptom frequency and severity on a 12-item, 0–5 scale (total 0–60), and (ii) be delivered and coded by non-specialists, making it highly suitable for LMIC implementation. It shows good reliability, validity and evidence of sensitivity [16]. Feasibility of such video-interaction coding in India was shown in the initial PASS pilot trial [9], and, in the PASS + pilot, BOSCC was used with 100% success at baseline (*n* = 40), and 35 participants successfully completed it at endpoint. In the PASS + pilot, the instrument development team from the US trained master trainers from UK and India ([name] and [name]), who undertook an adaptation for the South Asia context (including simplified behavioural descriptions and visual aids). They then trained project-based RAs. Coding of the BOSCC within the trial was shared by two project RAs and a master coder based in the USA. The inter-rater reliability (*n* = 16; comparing 2 trial RAs with the US master coder) gave an ICC of 0.80.

### Secondary outcomes

Parent–child communication will be measured using the Dyadic Communication Measure for Autism (DCMA) [17], a researcher-rated measure of parent–child social communication interaction used in both PASS and PASS + trials. This measures the proximal treatment outcomes reported in PASS, which were also demonstrated to mediate autism symptom outcome in the original UK trial.

Others secondary child and parent measures are listed below.

Child measures:Vineland Adaptive Behaviour Scales, Third Edition (Vineland 3), is a parent-rated measure of adaptive behaviour that is widely used to assess children with intellectual, developmental and other disabilities [18]Communication and Symbolic Behaviour Scales Developmental Profile (CSBS-DP) [19] is a measure of early communication and symbolic skills in young children that aims to identify those who have or are at-risk for developing a communication impairmentDevelopment Behaviour Checklist (DBC-P) [20] can be used for the assessment of behavioural and emotional problems of children and adolescents with development and intellectual disabilities. It is a questionnaire completed by parents or other primary caregiver and reports problems over a 6-month periodHealth status: parent-rated Child Health Utility-9D Index (CHU-9D), valued to allow calculation of QALYs [21]Paediatric Quality of life Inventory [Peds QL (2–4), (5–7), and (8–12)] is a modular approach to measuring health-related quality of life (HRQOL) in healthy children and adolescents and those with acute and chronic health conditionsScreening Tools for Autism Risk using Technology (START) developed by Sangath and other collaborators screens for autism risk in community setting using a digital application measuring attention disengagement, social attention and joint attention

Parent measures:Research on Autism and Families in India (RAFIN) [22] developed by Action for Autism, measures knowledge of autism, acceptance of the condition, empowerment and advocacy related to autism amongst parents of children with autism. This was removed in response to the COVID-19 pandemic (see below)Warwick-Edinburgh Mental Well-being Scale (WEMWBS) is a 14-item scale of mental well-being covering subjective well-being and psychological functioning in adolescents and adults, in which all items are worded positively and address feeling and functioning aspects of mental health.EQ-5D is a self-report measure of health status, with a descriptive system comprising five dimensions (mobility, self-care, usual activities, pain/discomfort, and anxiety/depression)

### Participant eligibility

The INCLEN Diagnostics Tool—Autism Spectrum Disorder (INDT-ASD), an indigenously developed tool for the assessment of Indian children, will be used to ascertain symptomology of ASD. Additionally, the Mullen Scale of Early Learning (visual reception and fine motor skills) will be also be used to establish participant eligibility and to characterise the sample’s development levels. This was replaced by the Vineland 3 later in the trial as explained in the following section.

### Baseline measures

Additionally, at baseline data on demographics (including child age, parent age and ethnicity, family SES), clinical information (date of ASD diagnosis, other medical diagnoses, schooling, interventions) and the home environment (including number of people in the household, number and age of siblings, language spoken) will also be collected.

